## Abstract

**Background:**

Hazardous drinking and posttraumatic stress disorder (PTSD) are commonly co-occurring conditions among adults. Motivational enhancement interventions, such as personalized feedback interventions (PFI), have demonstrated efficacy for reducing hazardous drinking. Emerging though scant literature has evaluated PFI for co-occurring PTSD and hazardous alcohol use. A transdiagnostic risk factor that may underlie this co-occurrence and inform novel PFI development is anxiety sensitivity (AS).

**Objective:**

To use a randomized controlled trial to evaluate the efficacy of a novel, computer-based PFI for hazardous drinkers with at least subclinical PTSD and elevated AS (AP-PFI), against a time-matched comparison condition (C-PFI).

**Methods:**

Participants (*N* = 100) will be recruited and enrolled from the Houston, TX community. The study includes: an in-person visit (baseline diagnostic assessment, a brief intervention, and a post-intervention assessment) and two follow-up assessments (1-week and 1-month). Participants who meet study inclusion criteria will be randomized to one of two conditions at baseline: AP-PFI or C-PFI. AP-PFI will consist of a brief, single-session, computer-delivered, PFI-based intervention that provides integrative and normative feedback about alcohol use, AS, and PTSD symptoms. C-PFI will be time-matched but will only include alcohol-related feedback.

**Conclusions:**

AP-PFI is designed to provide feedback about alcohol use, PTSD symptoms, and AS and their interplay and deliver psychoeducation on harm-reduction techniques, interoceptive exposure exercises, and stress management strategies. The intervention may address extant gaps in treatment for these co-occurring conditions by providing a brief, evidence-based, motivational enhancement intervention that is cost-effective with potential to be disseminated across a variety of healthcare settings.

## Introduction

1

Hazardous drinking (i.e., a pattern of alcohol use that increases risk for adverse health consequences) [1] and posttraumatic stress disorder (PTSD) are highly prevalent and commonly co-occurring conditions [2] that are associated with greater disability and poor health outcomes as compared to either condition alone [3,4]. More than 25% of United States (U.S.) adults endorse hazardous drinking, which is one of the leading causes of preventable death in the U.S [5]. and globally [6]. Individuals who experience PTSD symptoms are approximately three times more likely to engage in hazardous drinking compared to those without PTSD symptomatology [7]. Integrative models of hazardous drinking-PTSD co-occurrence suggest bidirectional and transactional effects between PTSD symptoms and the maintenance and/or exacerbation of alcohol use over time [8]. Consensus regarding best practices for treating co-occurring hazardous drinking-PTSD is lacking [9,10], and low treatment-seeking rates have been found among hazardous drinkers with PTSD [2].

Generally, research on the behavioral treatment of PTSD and co-occurring substance use disorders is a highly understudied area [11]. Personalized feedback interventions (PFI) may help to address this gap in the literature. Drawing on motivational and social perspectives, PFI motivate behavior change via psychoeducation and the presentation of personalized (e.g., profiles of current health behaviors, assessment of risk severity) and normative feedback (i.e., comparisons to relevant sociodemographic groups) [12,13]. PFI target misperceptions regarding an individual's behaviors and actual normative behaviors, highlight consequences of these behaviors, and offer strategies for modifying them. PFI have demonstrated efficacy in reducing hazardous drinking and alcohol-related consequences across various populations [[14], [15], [16]] and offer a brief, cost-effective, easily disseminable [17] avenue for providing feedback and reducing alcohol use and consequences.

Given that PTSD symptoms may impede drinking reduction [18], and that hazardous drinkers with PTSD symptoms likely experience unique challenges to modifying their drinking [19] due to their increased reliance on alcohol to regulate negative emotional states, it is necessary to develop brief interventions that address hazardous drinking among trauma-exposed adults with PTSD symptoms. Accordingly, recent PFI work among military veterans with PTSD has evinced preliminary promising results on hazardous drinking and PTSD symptoms [16,[19], [20], [21]]. However, only three of these studies have explicitly integrated PTSD- and alcohol-focused personalized feedback and examined its impact on reducing hazardous drinking and PTSD symptoms [[19], [20], [21]]. Although these studies utilized either an app-based approach [19] or a single-session in-person format [20], no study to date has integrated these modalities into a single-session, comprehensive intervention for non-veteran, community adults. Moreover, it is important to consider malleable factors that underlie hazardous drinking-PTSD relations to enhance the efficacy of personalized evidence-based interventions.

One such transdiagnostic factor with established relevance to both hazardous drinking and PTSD is anxiety sensitivity (AS) [22]. AS, defined as the fear of anxiety-related sensations and cognitions (e.g., concerns related to increased heart rate and/or racing thoughts) [23,24], is a malleable [25], cognitive-affective vulnerability risk factor that is conceptually distinct from both trait anxiety [26] and PTSD [27]. AS has been positively related to hazardous drinking [[28], [29], [30]] and coping-oriented drinking motives across various populations [[31], [32], [33], [34]] and is related to increased rates of consumption and alcohol use disorder (AUD) [35,36]. Further, AS is implicated in the development and maintenance of PTSD [[37], [38], [39]] and may underlie hazardous drinking-PTSD comorbidity by amplifying PTSD symptomatology (e.g., hyperarousal) and motivating drinking to down-regulate such affect [22,40,41]. Despite the efficacy of AS interventions for reducing hazardous drinking [42] and PTSD symptoms [43], an integrated intervention to specifically target AS in the context of hazardous drinking and PTSD symptoms has not been developed or tested.

The objective of the present study is to examine the feasibility, acceptability, and efficacy of a novel PFI among hazardous drinkers with at least subclinical PTSD (i.e., endorsing at least two symptoms in each PTSD symptom cluster) and elevated AS. Hazardous drinkers with at least subclinical PTSD and elevated AS (*N* = 100) recruited from the community will be randomly assigned to receive Alcohol-PTSD-PFI (AP-PFI; *n* = 50) or active comparison condition (C-PFI; *n* = 50). The AP-PFI will provide feedback about alcohol use in the context of PTSD symptoms, PTSD-alcohol interplay, AS, and coping-oriented drinking. Primary outcomes include intervention-related perceived satisfaction and credibility/expectancies, drinking motivational factors (e.g., expectancies) and alcohol-related behaviors (e.g., cravings and consumption) and secondary outcomes include changes in AS and PTSD and exploring theoretically relevant mediators/moderators. Specific aims and hypotheses are described in Section 2.2.

## Method

2

### Trial design overview

2.1

The study is funded by the National Institute on Alcohol Abuse and Alcoholism (NIAAA; F31AA029600) and is registered on clinicaltrials.gov (ID: NCT04836442). Enrollment to the pilot randomized controlled trial (RCT) began in May 2021 and, as of this writing, is in the recruitment phase. This study will employ a longitudinal experimental design and include the following timepoints: (1) screening, (2) baseline assessment, (3) computer-delivered, one-session intervention (participants randomized to AP-PFI or C-PFI), (4) post-intervention follow-up assessment, (5) 1-week follow-up assessment, and (6) 1-month follow-up assessment.

### Specific aims and hypotheses

2.2

The first aim of this project will be to evaluate the feasibility and acceptability of a brief, single-session, integrated, computer-based PFI (AP-PFI) based on participant ratings of satisfaction and the perceived credibility/expectancies of the intervention. The second aim will be to conduct a RCT to examine the efficacy and intervention effects on drinking, AS, and PTSD outcomes of AP-PFI, versus C-PFI, across the post-intervention and 1-week and 1-month follow-ups. The third aim will be to explore mechanisms of change and moderators.

Regarding the first aim (feasibility and acceptability), it is hypothesized that participants randomized to AP-PFI (vs. C-PFI) will evince greater satisfaction and perceived credibility/expectancies of the intervention. Regarding the second aim (efficacy and intervention effects), it is hypothesized that participants randomized to AP-PFI (vs. C-PFI) will evince (1) greater motivation/intention to reduce drinking, (2) lower levels of AS, (3) lower frequency and quantity of alcohol consumption, (4) reduced negative consequences of drinking and alcohol-related craving, and (5) lower PTSD symptom severity at 1-week and 1-month follow-up. Additionally, regarding the third aim, it is hypothesized that the effects of AP-PFI (vs. C-PFI) on post-intervention outcomes will be mediated by greater motivation/intention to reduce drinking and lower levels of AS. It is also hypothesized that the effects of AP-PFI (vs. C-PFI) on post-intervention, 1-week, and 1-month follow-up outcomes will be moderated by biological sex (i.e., larger magnitude of effect among female participants, relative to male participants) and family history of AUD (i.e., larger magnitude of effect among participants with a family history of AUD).

### Participant recruitment and eligibility

2.3

The proposed study will include 100 hazardous alcohol users with PTSD symptoms and elevated AS recruited from the Houston, Texas community. Potential participants will be assessed for inclusion/exclusion criteria via an online screener and during the baseline appointment. Inclusion criteria will include the following: (1) ≥21 years of age (demographics questionnaire), (2) current hazardous drinking (Alcohol Use Disorders Identification Test cut-off scores of ≥8 for males and ≥7 for females [44,45]), (3) lifetime exposure to a *Diagnostic and Statistical Manual of Mental Disorders, Fifth Edition* (*DSM-5*) Criterion A traumatic event (Life Events Checklist for *DSM*-5) and endorsing ≥2 symptoms in each *DSM-5* PTSD symptom cluster (PTSD Checklist for DSM-5 [46]), (4) elevated AS score (≥17 on Anxiety Sensitivity Index-3 [47]), and (5) fluency in English (demographics questionnaire). Exclusion criteria will include the following: (1) concurrent alcohol or other substance use treatment (demographics questionnaire), (2) current/past bipolar or psychotic disorder (demographics questionnaire), (3) current imminent risk of suicide (i.e., past-month suicidal ideation with intent/plan; Beck Suicide Scale), (4) current pregnancy (demographics questionnaire), (5) inability to provide verbal or written consent, and (6) breath analysis estimating blood alcohol concentration (BAC) above 0 at baseline (Alco-Sensor FST Breath Alcohol Tester). Participants with non-zero BAC at baseline will be rescheduled for another baseline appointment.

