### Procedures

2.4

Participants will be recruited from the Houston community through multimedia platforms (university listservs, flyers, etc.). Interested participants will complete an online screener via Qualtrics, an online data collection platform. Participants who qualify will be contacted by trained study staff who will describe the study and schedule the baseline visit. Upon arrival to the lab, participants will provide informed consent and be assessed regarding trauma history, PTSD symptomatology, substance use, and the presence of current/past bipolar or psychotic disorder, as determined by the MINI-International Neuropsychiatric Interview. A urine drug screen will be implemented at baseline to identify current substance use (not used for exclusion).

Once eligibility is confirmed, participants will be randomly assigned (equally; 50 participants per condition, using a simple randomization design) to AP-PFI or C-PFI and complete the intervention/comparison condition on laboratory computers. Participants will then complete a post-intervention assessment. Online follow-up assessment will include similar surveys and will be scheduled 1-week and 1-month after completing the intervention conditions. Participants will be compensated $25 for completing the in-person baseline assessment and $35 and $40 for completing the 1-week and 1-month follow-up surveys, respectively, for a total of $100 in eGift cards. All study procedures were approved by the University Institutional Review Board and all study measures and assessment procedures are outlined in Table 1 and Fig. 1.

**Table 1 tbl1:** Study measures and timepoints.

Measures	Items	Assessment Timepoint				
		**Screen**	**Baseline**	**Post**	**1-Week**	**1-Month**
Demographics Questionnaire	**20**	**X**				
Urinalysis drug screening	**N/A**		**X**			
Breath analysis	**N/A**		**X**			
MINI-International Neuropsychiatric Interview	**Variable**		**X**			
Treatment Credibility/Expectancy Questionnaire	**6**			**X**		
Modified Satisfaction with Treatment	**7**			**X**		
Alcohol Ladder	**1**		**X**	**X**	**X**	**X**
Modified Alcohol Use Disorders Identification Test	**3**–**10**	**X**	**X**		**X**	**X**
The Short Inventory of Problems	**15**		**X**		**X**	**X**
Alcohol Urges Questionnaire	**8**		**X**	**X**	**X**	**X**
Timeline Follow-Back	**30**		**X**		**X**	**X**
Life Events Checklist for *DSM-5*	**17**	**X**	**X**		**X**	**X**
Modified PTSD Checklist for *DSM-5*	**20**	**X**	**X**		**X**	**X**

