Anxiety Sensitivity Index-3	**18**	**X**				
The Short Scale Anxiety Sensitivity Index	**5**		**X**		**X**	**X**
The Beck Suicide Scale	**21**	**X**	**X**		**X**	**X**

*Note.* MINI-International Neuropsychiatric Interview (MINI) [49]; Treatment Credibility/Expectancy Questionnaire (TCEQ) [58]; Modified Satisfaction with Treatment (SAT) [59]; Alcohol Ladder [53]; Alcohol Use Disorders Identification Test (AUDIT) [1], modified timeframe to correspond with each follow-up timepoint; The Short Inventory of Problems (SIP) [54]; Alcohol Urges Questionnaire – Short Form- Revised (AUQ) [55]; Timeline Follow-Back (TLFB) [52]; Life Events Checklist for DSM-5 (LEC-5) [50]; PTSD Checklist for DSM-5 (PCL-5) [46], modified timeframe to correspond with each follow-up timepoint; Anxiety Sensitivity Index-3 [56]; Short-Scale Anxiety Sensitivity Index (SSASI) [47]; Beck Suicide Scale (BSS) [57].

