#### Diagnostic measure

2.6.2

*MINI-International Neuropsychiatric Interview* (MINI) [49]. The MINI is a brief, structured, clinician-administered diagnostic interview to thoroughly assess common *DSM-5* disorders using *DSM-5* diagnostic guidelines. Trained doctoral students will conduct diagnostic assessments and will be supervised regarding the accuracy of their diagnosis by the principal investigator and doctoral-level raters. The MINI will be administered at baseline and will be used to assess if any exclusionary criteria are met and will serve to document psychopathology within the sample.

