#### Affective measures

2.6.5

*Short-Scale Anxiety Sensitivity Index* (SSASI) [47]. The SSAI is a 5-item self-report measure that assesses anxiety-related interoceptive sensations and cognitions. The SSASI was derived from the original 18-item *Anxiety Sensitivity Index-3 (ASI-3)* [56]. Each item is rated using a 4-point Likert scale (0 = *Very little* to 4 = *Very much*) in regard to how much a respondent agrees with the specific statement being rated, with higher scores indicating greater severity of AS. For the current study, the total score of the SSASI (i.e., the sum of all 5 items) will be used to indicate the severity of an individual's AS and will be administered at each timepoint (except the post-intervention assessment) and the total score of the ASI-3 will be used to assess study inclusion criteria (elevated AS score [≥17]) during the screening timepoint.

*Beck Suicide Scale* (BSS) [57]. The BSS is a 21-tem, self-report measure that assesses the severity of an individual's suicidal ideation or desire to die. Respondent's rate, on a 3-point scale, the most accurate statement for the intensity of past-week suicidal ideation (e.g., “I have no wish to live”), with higher summed total scores indicating more severe suicide ideation. The BSS will be administered at each timepoint (except the post-intervention assessment) to assess suicide risk**.**

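### The suicide-risk exclusion looks back a month, but the scale named to apply it is described as rating only the past week

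*Protocol article*

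**What the plan says.** Exclusion criterion 3 in Section 2.3 concerns current imminent risk of suicide. The bracket that defines it reads "past-month suicidal ideation with intent/plan; Beck Suicide Scale", so it gives both a look-back period of one month and the instrument.

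Section 2.6.5 says that respondents to the Beck Suicide Scale (BSS) choose "the most accurate statement for the intensity of past-week suicidal ideation". On timing it states: "The BSS will be administered at each timepoint (except the post-intervention assessment) to assess suicide risk". Table 1 agrees, marking the scale at screening, baseline, 1 week and 1 month. Two administrations therefore precede randomization.

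Two statements concern the baseline MINI. Section 2.4 ties it to "the presence of current/past bipolar or psychotic disorder, as determined by the MINI-International Neuropsychiatric Interview". Section 2.6.2 says more broadly that it "will be used to assess if any exclusionary criteria are met". Neither mentions suicide risk.

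**The concern.** A criterion can be applied as written only if the instrument that decides it looks back at least as far as the criterion does. Here the criterion reaches back a month and its named instrument, as described, a week. Ideation with intent or a plan in the earlier part of the month meets the exclusion but lies outside what the scale asks about.

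This is the only suicide-related exclusion in the list. The population is trauma-exposed, drinks hazardously and has elevated anxiety sensitivity, and after one laboratory visit it is followed by online survey. Staff could also apply the rule unevenly, some by the wording of the criterion and some by the wording of the scale. Section 2.1 says that recruitment was under way at the time of writing, so a correction could still affect who is enrolled.

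**Working it through.** There is no trial figure to reproduce. The check sets the statements side by side and counts days.

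**Inputs**
- Look-back of the criterion: past month (Section 2.3). Taken as 30 days, which is an assumption.
- Look-back of the BSS as described: past week, or 7 days (Section 2.6.5).
- Administrations before randomization: two, at screening and at baseline (Section 2.6.5, Table 1).
- Interval from screening to baseline: not stated, so treated as a range. Call it *s* days.

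**One administration**
- Covered: 7 of 30 days, 7/30 = 23%.
- Not covered: 30 − 7 = 23 days, 23/30 = 77%.

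**Both administrations, counted over the 30 days before baseline**
- The baseline scale covers days 1 to 7 before baseline. The screening scale covers the 7 days before screening, that is, from *s* to *s* + 7 days before baseline.
- Least coverage: screening and baseline fall together (*s* near 0), or screening lies 30 or more days back. The screening scale then adds nothing within the window. Covered: 7 days. Not covered: 23 days, 77%.
- Most coverage: *s* is between 7 and 23, so the two weeks do not overlap and both lie inside the window. Covered: 7 + 7 = 14 days. Not covered: 30 − 14 = 16 days, 16/30 = 53%.
- For no value of *s* does the scale as described cover the whole window.

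**Is another version of the scale described?** None is. The article does state such changes for other measures: Section 2.6.3 gives past-month and past-week versions of the PCL-5, and Section 2.6.4 gives modified timeframes for the AUDIT, the Timeline Follow-Back and the Short Inventory of Problems. For the BSS, Section 2.6.5 gives only the past week. The note to Table 1 also marks no modification for the BSS. Little weight can rest on that, because the same note omits modifications that the text does state for other measures.

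**Does the MINI close the gap?** Section 2.6.2 gives it a general role in checking exclusions, and Section 2.4 links it to bipolar and psychotic disorder. No section links it to suicide risk or gives a recall period for that purpose. It is given only at baseline, so it cannot apply the criterion at the online screener. It may be a further check, but the article does not establish that it is.

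**The case against.** The strongest reply is that passing one scale is not the same as entering the trial. Section 2.3 does not always name every source for a criterion. For bipolar or psychotic disorder it names only the demographics questionnaire, yet Section 2.4 has the MINI determine this at baseline. Read plainly, the general statement in Section 2.6.2 takes in the suicide-risk exclusion too. Nor can the list of baseline assessments in Section 2.4 be used to narrow it, because that list leaves out the BSS, which Table 1 schedules at baseline. This stands as far as it goes. A reader might infer that anyone with intent or a plan earlier in the month would be enrolled, and the article does not support that. Such a person must pass the scale twice and also an interview that may look for the same thing. What the reply cannot show is that the interview does so, or over what period.

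Second, the construct is current imminent risk, on which a past-week rating bears directly. The month appears only in the explanatory bracket. The scale is also repeated at both follow-ups. So it would be wrong to infer that the trial lacks a suicide-risk check. The mismatch concerns the earlier part of the stated window. But the bracket is the operational definition of the exclusion, and its window is not the one described for its instrument.

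Third, a condensed article commonly leaves the handling of a positive screen to the full protocol. That is fair, and no such detail is asked for here. The point is that two statements in the article disagree, which brevity does not explain.

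**Conclusion.** The point holds as a contradiction between a safety exclusion and the instrument named to apply it. As described, the BSS leaves about 16 to 23 of the 30 days before baseline (53% to 77%) unassessed. Its position in that range depends on the unstated interval from screening to baseline. The result assumes a 30-day month and that the scale is used with the recall period the article gives.

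A person whose intent or plan fell 8 to 30 days before baseline could pass the named check if those days also fall outside the week rated at screening. The percentages count calendar days, not missed risk, and the number of people affected cannot be derived. The MINI may narrow the gap, but the article does not say so. Sample size, power and the efficacy analysis are not touched. The correction is still worth making, because it concerns participant safety during recruitment and costs very little.

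**What to change.** Reconcile Sections 2.3 and 2.6.5 so that the recall window of exclusion 3 and that of the instrument that applies it are the same. If the baseline MINI is also relied on for this criterion, name it in Section 2.3 beside the BSS. Which window applies is a clinical decision for the trial team, and this review takes no position on it.

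The cost is a change of protocol wording and, at most, a changed recall instruction on a questionnaire already given at screening and baseline. No new visit or measure is needed, and the analysis does not change.
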